### Sample and ethics

A total of 30 trainee therapists and 150 patients will be recruited at the CPP. Enlisting as a trainee in the clinic is preceded by a rigorous assessment that evaluates the potential trainee’s personal suitability for becoming a CBT therapist.

The general inclusion criterion for patients is a primary depressive- or anxiety-disorder diagnosis in the Structured Clinical Interview according to the DSM-5 criteria (Falkai et al. 2014). We chose these two disorder groups because from patients being treated at German university therapy-training centers; approximately 40 % suffer from a primary major depression, and approximately 30 % suffer from a primary anxiety disorder (e.g. (Nelson and Hiller 2013)). Hence, our results will be of importance to a majority of outpatient diagnostic groups.

The general exclusion criteria for patients will be as follows: (1) an age below 18 or above 65 years, (2) insufficient German language skills, (3) those suffering from a psychotic disorder, (4) current suicidal risk. Comorbidities with disorders not on the exclusion list are generally not considered as limitations to entering the study, as long as depression and anxiety disorders are of primary concern.

Power analyses with G*Power (Faul et al. 2007) for the detection of small effects (Cohen’s *f* = 0.12) for the interaction between time (pre, mid-5, mid-15, post) and treatment condition (TAU-M versus TAU-PMR versus TAU) (ANOVA repeated measures, within-between-interaction, α = 0.05, power = 0.80, number of groups = 3, number of measurements = 4, pre-post correlation *r* = 0.05, nonsphericity correction = 1) along with practical clinical considerations (Flückiger 2014) resulted in a sample size of 123 patients. Taking potential dropouts into account, a total sample of 150 patients will be assigned to one of the three groups by a stratified randomization process. Patients will be stratified into one of two categories: one group with the main diagnosis of major depression and the other group with the main diagnosis of an anxiety disorder.

Voluntary participation and written, informed consent are necessary conditions for participation in the study. The local ethics committee (Ethikkommission der Fakultät für Verhaltens- und Empirische Kulturwissenschaften der Universität Heidelberg) approved the study protocol in accordance with the Helsinki Declaration.

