### Objectives

The main purpose of this study is to identify whether exercises with mindfulness elements carried out at the beginning of individual therapy sessions help to improve the therapeutic process under effectiveness conditions. Consequently, we designed a study to analyze the effects of a 5-min session-introducing intervention with mindfulness elements (SIIME) conducted together by trainee therapists and their patients in a randomized, controlled, longitudinal design under naturalistic conditions with PMR as the active control group.

More specifically, we will examine the effects of SIIME practiced by both outpatients and CBT trainee therapists at the beginning of the 25 therapy sessions (brief-term CBT of the German healthcare system) on (a) therapeutic alliance measured on a session-to-session basis and (b) on clinical outcomes assessed every 10 sessions. Thus, before the start of therapeutic treatment, patients are randomized into a treatment-as-usual + mindfulness intervention group (TAU + M) practicing SIIME, a TAU + PMR-control group practicing a session-introducing short form of PMR, or a TAU control group without standardized session-introducing intervention. Before the start of the intervention study, all therapists will participate in a 6-week workshop-based mindfulness and PMR program. We will investigate the following hypotheses:We hypothesize that both patients and therapists of the TAU + M will experience higher levels of therapeutic alliance compared to the TAU + PMR and TAU.We hypothesize that in the TAU + M, there will be stronger reductions in clinical symptomatology of patients compared to the TAU + PMR and TAU.

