**Session questionnaire-patients**						
Working Alliance Inventory- Short Revised- Patient (WAI-SR-P)		1–25				
Therapist Presence Inventory-Patient-Short (TPI-P-S)		1–25				
Practice Quality-Mindfulness-Patient-Short (PQ-M-P-S)		1–25				

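### The sample-size statement promises small effects, but f = 0.12 corresponds to roughly 0.6–0.7 SD between arms, the printed r = 0.05 does not give N = 123, and the alliance outcome is not covered

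*Protocol article*

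**What the plan says.** The protocol article gives one sample-size calculation, in Sample and ethics. It is described as being "for the detection of small effects", with Cohen's f = 0.12, "for the interaction between time (pre, mid-5, mid-15, post) and treatment condition (TAU-M versus TAU-PMR versus TAU"), using a G*Power routine labelled "ANOVA repeated measures, within-between-interaction" with "α = 0.05, power = 0.80, number of groups = 3, number of measurements = 4" and "pre-post correlation *r* = 0.05, nonsphericity correction = 1". Together with practical clinical considerations, this is said to lead to 123 patients, raised to 150 for dropout.

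The hypotheses are worded differently. Under Objectives, patients and therapists in TAU + M "will experience higher levels of therapeutic alliance compared to the TAU + PMR and TAU", and TAU + M is expected to show a stronger symptom reduction than each control. Statistical analysis then sets out a three-level model. It plans three-arm comparisons of intercepts and slopes, and states the directional expectation that TAU + M is better than TAU + PMR and TAU on both.

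Primary outcome measures lists two outcomes: alliance (WAI-SR) first and the BSCL Global Severity Index (GSI) second. Table 1 schedules the BSCL at pre, mid-5, mid-15, post and follow-up. The row "Working Alliance Inventory- Short Revised- Patient (WAI-SR-P") and its therapist counterpart are scheduled at sessions 1–25 only, with no Pre entry.

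**The concern.** Most readers will take a statement about small effects to describe the difference between arms, conventionally about 0.2 SD. In a 3 × 4 interaction, f averages the interaction effect over 12 cells, so a small f can go with a much larger separation at the end of treatment. The test that was sized is also not the pairwise comparison that the hypotheses name. Its four-wave layout fits only the second primary outcome. Finally, a between-wave correlation of 0.05 is surprisingly low for repeated symptom scores, so the printed N needs checking.

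What is at stake is interpretation. A non-significant result against PMR, an active control of equal duration and similar wording, could be read as excluding a small benefit that the trial had little chance of detecting.

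**Working it through.** **Inputs.** From Sample and ethics: f = 0.12, k = 3 arms, m = 4 waves, α = 0.05, power 0.80, r = 0.05, nonsphericity correction 1, N = 123 (41 per arm) and 150 (50 per arm). My assumptions: the pattern of separation, compound symmetry, and r = 0.5 as the alternative correlation. SD means the within-cell SD. Therapist clustering and multiplicity are ignored, as in the article.

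**1. The plan's own figure.** G*Power's default for this test uses λ = f²·N·m/(1 − r), df1 = (k − 1)(m − 1) = 6 and df2 = (N − k)(m − 1) = 360 at N = 123.

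| r | λ at N = 123 | Power at 123 | Power at 150 | N for 80% |
|---|---|---|---|---|
| 0.05 (printed) | 0.0144 × 123 × 4 / 0.95 = 7.46 | 49% | 59% | 227 (228 in equal arms) |
| 0.5 | 0.0144 × 123 × 4 / 0.5 = 14.17 | 81% | 89% | 121 (123 in equal arms) |

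The printed inputs do not give 123; r = 0.5 does, once rounded to equal arms. Two other conventions for λ, with the printed inputs, give 321 and 318. Keeping r = 0.05 and using f = 0.165 would also give 121 (123), so a wrong r is the likeliest explanation but not the only arithmetical one.

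**2. From f to a difference between arms.** Let D be the session-25 difference, g the arm pattern and t the time pattern (0 at pre, 1 at post). Then f = D·√(var(g)·var(t)), with variances taken over the 3 arms and 4 waves (divisor 3 or 4). For TAU + M against two equal controls, g = (1, 0, 0) and var(g) = 2/9 = 0.2222.

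| Time pattern | var(t) | f/D | D at f = 0.12 |
|---|---|---|---|
| Linear by wave (0, 1/3, 2/3, 1) | 0.1389 | 0.1757 | 0.68 SD |
| Linear by session (0, 0.2, 0.6, 1) | 0.1475 | 0.1810 | 0.66 SD |
| Step from session 5 (0, 1, 1, 1) | 0.1875 | 0.2041 | 0.59 SD |
| From session 15 only (0, 0, 1, 1) | 0.2500 | 0.2357 | 0.51 SD |

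With arms evenly spaced, the two outermost arms differ by 0.59–0.79 SD, and neighbouring arms by half that. None of these conversions depends on r. In the other direction, D = 0.2 SD (linear by wave) is f = 0.2 × 0.1757 = 0.035. The omnibus test at N = 123 then has 10% power if r = 0.5 and 8% if r = 0.05.

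**3. The hypothesised contrast.** For TAU + M against one control, the standard error of the slope difference, scaled to session 25, is √(2(1 − r)/(n·Sxx)). Sxx = 4 × var(t), which is 0.556 by wave and 0.590 by session. At r = 0.5 and n = 41:

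- by wave: √(1/(41 × 0.556)) = 0.210; detectable difference 2.80 × 0.210 = 0.59 SD
- by session: √(1/(41 × 0.590)) = 0.203; detectable difference 2.80 × 0.203 = 0.57 SD

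Noncentral-t calculations give 0.59 and 0.58. With n = 50 the normal approximation gives 0.53 and 0.52 SD. At n = 41, power is about 16% for 0.2 SD, 29–31% for 0.3 SD and 89–90% for 0.67 SD. With the printed r = 0.05 and n = 41, the detectable difference is 0.80–0.82 SD.

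**4. Alliance.** With no Pre value and 25 sessions, the WAI-SR cannot enter a pre/mid-5/mid-15/post layout. An interaction calculation also says nothing about a difference in level. As a guide, take the mean over 25 sessions, with an assumed between-patient share of variance (ICC) of 0.6–0.8. Then SE = √(2(ICC + (1 − ICC)/25)/41) = 0.173–0.198, and the detectable difference is 2.80 × SE = 0.49–0.56 SD.

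**The case against.** The authors attach the word small to a disclosed f and claim nothing about 0.2 SD or any pairwise difference. That stands. A reader might infer that the design cannot detect the effect it claims; at r = 0.5 it has 81% power for f = 0.12, so the documents do not support that reading. The fault is that the label misleads about differences between arms.

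The SD conversion depends on a pattern that the article does not give. That also stands, so the figure must carry its assumption and its range.

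A reader might infer that sizing on an omnibus test weakens the pairwise comparisons. It does not: Statistical analysis also plans the three-arm interaction, and at 0.67 SD the one-degree-of-freedom slope contrast has 89–90% power at r = 0.5. What is missing is a stated detectable difference for the contrasts.

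A reader might infer that alliance is the worse-powered outcome. Under the assumptions above it is no worse placed than GSI (0.49–0.56 against 0.57–0.59 SD). A condensed article may also leave separate power statements to a fuller document. But the one justification it prints, for a trial with two primary outcomes, fits only the second.

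Finally, practical considerations are said to have contributed to the 123, so it need not be pure G*Power output. The article does not say what they changed, and the stated 80% power still does not follow from the stated r.

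**Conclusion.** The concern holds as a misdescription of sensitivity together with a sample-size figure that does not reproduce. It does not show that the trial is too small. If TAU + M separates from two equal controls, f = 0.12 is about 0.6–0.7 SD at session 25 (about 0.5–0.8 SD over the other patterns tried), which is medium by the usual convention. At 123 analysable patients, the pairwise GSI slope contrast detects about 0.6 SD with 80% power if r = 0.5, and about 0.8 SD if r = 0.05 was really meant. Neither the first primary outcome nor the level hypothesis has a stated power basis.

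The 49% power at N = 123 applies only if r = 0.05 is taken literally. A reader might infer that the trial has coin-flip power, but the near-exact match at r = 0.5 points to a misprint. All these figures rest on compound symmetry and ignore clustering by therapist and multiplicity.

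**What to change.** First reconcile r with N = 123: correct r, or, if 0.05 was intended, restate the power for f = 0.12 as about 49% at 123. No replacement wording is safe until this is settled.

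Then delete the small-effects wording. For TAU + M against TAU + PMR and TAU + M against TAU, on each primary outcome, state the detectable difference under the planned multilevel model, with the assumed pattern and correlation. For GSI at 123 analysable patients, this is about 0.6 SD if r = 0.5 and about 0.8 SD if r = 0.05. For WAI-SR, base it on the session-by-session schedule and the level hypothesis.

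The planned 150 patients can stay. The cost is a few sentences and a less favourable stated figure.

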### Primary outcome measures

Primary outcome measure 1: To assess the quality of the therapeutic alliance, we will apply the Working Alliance Inventory- Short Revised (WAI-SR; (Hatcher and Gillaspy 2006)). The WAI-SR is a 12-item self-report instrument with patient and therapist perspectives rated on a seven-point scale. It includes three subscales: bond, goals, and tasks. The bond subscale reflects the emotional relationship between patient and therapist. The goals and tasks subscales refer to the agreement of patients and therapists concerning the treatment goals and tasks. The WAI-SR is considered the gold standard for alliance assessment, has excellent psychometric properties, and is outcome predictive, as has been demonstrated in meta-analyses (e.g. (Horvath et al. 2011)).Primary outcome measure 2: To assess general symptom severity, the Global Severity Index (GSI) of the Brief Symptom Checklist (BSCL; (Derogatis and Melisaratos 1983; Franke 2000)) will be applied. The BSCL is the short version of the Symptom-Checklist-90-Revised (SCL-90-R; (Derogatis and Lazarus 1994)) and consists of 53 items forming nine subscales as follows: somatization, obsessive-compulsive, interpersonal sensitivity, depression, anxiety, hostility, phobic anxiety, paranoid ideation, and psychoticism, which are rated on a five-step scale. It showed excellent internal consistencies, with 0.71 ≤ α ≤ 0.85; good retest reliabilities, with 0.68 ≤ *r* ≤ 0.91; high correlations to the original SCL-90-R, with 0.92 ≤ *r* ≤ 0.99; and good construct validity, with scale-outcome correlations between 0.30 ≤ *r* ≤ 0.72.

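### The printed power inputs do not give 123 patients: with a correlation of 0.05 that number has about 49% power, and the figure of 123 appears only when the correlation is 0.50

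*Protocol article*

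**What the plan says.** The section Sample and ethics gives the article's only sample-size justification. The calculation is "for the detection of small effects" (Cohen's f = 0.12) on the interaction between time (four waves) and treatment condition (three arms). The settings are "ANOVA repeated measures, within-between-interaction, α = 0.05, power = 0.80, number of groups = 3, number of measurements = 4", followed by "pre-post correlation *r* = 0.05, nonsphericity correction = 1". These inputs, with a reference to practical and clinical grounds, "resulted in a sample size of 123 patients". The total is then raised to 150 to allow for dropouts; no dropout rate is given, but 1 − 123/150 = 18%.

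**The concern.** The paragraph states every input that the calculation needs, so the result can be checked without any further document. A correlation of 0.05 between repeated measurements is unusually low. In this type of test it is also costly, because the noncentrality is proportional to 1/(1 − r). If the inputs are correct as printed, the total should be close to twice 123 and the trial does not have the power that it claims for its slope hypothesis. If the correlation is misprinted, the sample size may be sound but the record of how it was obtained is wrong. Either way, a reader who re-runs the line will conclude that the trial is about half the required size.

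**Working it through.** **Inputs, all from Sample and ethics:** f = 0.12; alpha = 0.05; target power = 0.80; k = 3 groups; m = 4 measurements; r = 0.05; nonsphericity correction ε = 1; stated N = 123.

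**Formulas** (G*Power, repeated-measures ANOVA, within-between interaction):

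- λ = f² · N · m · ε / (1 − r)
- df1 = (k − 1)(m − 1)ε = 2 × 3 = 6
- df2 = (N − k)(m − 1)ε = 3(N − 3)
- power = P(F′ > F₀.₉₅(df1, df2)), where F′ is noncentral F with noncentrality λ

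**Attempt to reproduce 123 with r = 0.05.** At N = 123, λ = 0.0144 × 123 × 4 / 0.95 = 7.0848 / 0.95 = 7.46, df2 = 360 and the critical F is 2.124. Power is 0.489, so the stated figure is not reproduced.

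**The same calculation at other totals and with r = 0.50:**

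| r | N | λ | df2 | Power |
|---|---|---|---|---|
| 0.05 | 123 | 7.46 | 360 | 0.489 |
| 0.05 | 150 | 9.09 | 441 | 0.588 |
| 0.05 | 226 | 13.70 | 669 | 0.798 |
| 0.05 | 227 | 13.76 | 672 | 0.800 |
| 0.05 | 228 | 13.82 | 675 | 0.802 |
| 0.50 | 120 | 13.82 | 351 | 0.798 |
| 0.50 | 121 | 13.94 | 354 | 0.802 |
| 0.50 | 123 | 14.17 | 360 | 0.810 |
| 0.50 | 150 | 17.28 | 441 | 0.892 |

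With r = 0.05, 80% power needs 227 patients, or 228 in three arms of 76. With r = 0.50 it needs 121, and the smallest multiple of three that suffices is 123 (three arms of 41).

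**Detectable effect with r = 0.05.** The f that gives 80% power is 0.164 at N = 123 and 0.148 at N = 150, against the stated 0.12.

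**Could another setting explain 123 while r stays at 0.05?** Power at N = 123 under each alternative:

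- alpha 0.10: 0.62
- two groups, four measurements: 0.62; two groups, five measurements: 0.68
- three groups, five measurements: 0.54
- test of the within-subject main effect: 0.61; of the between-subject main effect: 0.58
- λ computed with m − 1 in place of m: 0.37
- definitions of λ without the correlation term: 0.13 to 0.34

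None reaches 0.80.

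**Other correlations, as a check on the r = 0.50 match.** Required totals in equal arms are 147 (r = 0.40), 135 (0.45), 123 (0.50) and 111 (0.55). Of these values only 0.50 gives 123.

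**The case against.** The strongest reply is that this is a slip in reporting and not an underpowered design. Changing one input to 0.50 returns 123 exactly, which suggests that the calculation was run properly and the value was mistyped. On that reading the sample size, the 80% power and the target of 150 all stand for this calculation, and nothing in the conduct or analysis of the trial changes. That is the likeliest explanation, and it decides how the conclusion should be worded. It does not remove the error: the printed input and the printed power contradict each other, and only the authors can say which one is wrong.

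A second reply is that the article attributes 123 partly to practical and clinical grounds. Such grounds could justify recruiting fewer patients than the calculation asks for, but they cannot make power 0.80 true at that number. The exact match at r = 0.50 also makes it plausible that 123 is plain software output.

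A third point concerns supporting evidence. The section Primary outcome measures reports "good retest reliabilities" of 0.68 to 0.91 for the BSCL, which makes 0.05 look implausibly low. This is weak evidence. Retest stability is not the correlation across 25 sessions of treatment, the range is not attributed to the Global Severity Index, and it does not point to 0.50 either: r = 0.68 would need only 78 patients. The conclusion does not rest on it.

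**Conclusion.** The concern holds. As printed, the inputs give 49% power at 123 patients and 59% at 150, not 80%, and the required total is 228 in equal arms. With r = 0.50 the stated 123 is reproduced exactly, with power 0.81, so a misprinted correlation is the probable cause but is not established. The result assumes G*Power's default definition of f for this test and takes all the other inputs as stated; no variant tried with r = 0.05 rescues the figure. The allowance for dropouts does not cover the gap, since power stays at 0.588 even if all 150 patients are analysed. Because this is the only justification of the sample size, the line has to be corrected whichever reading is true.

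**What to change.** Check the saved G*Power output and state which correlation was used.

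- **If it was 0.50:** replace 0.05 with 0.50 in the sample-size paragraph, and preferably add the basis for expecting that correlation between waves of the outcome being powered. The 123 and the 150 then remain as they are.
- **If it was 0.05:** withdraw the 80% claim. Restate power for f = 0.12 as about 49% at 123 patients and 59% at 150, or equivalently give the detectable f at 80% power as 0.164 and 0.148. Keeping 80% power at f = 0.12 would instead require 228 analysable patients before any allowance for dropouts.

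The first correction costs one figure. Restating the power in the second case changes a sentence and needs no extra patients, but it leaves the 80% target unmet; only keeping that target would mean more recruitment.

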### Mindfulness workshop training

To prepare the 30 trainee therapists for the SIIME outlined in the next section, we will first offer two workshops separated by a 6-week home-practice interval to all trainee therapists participating in the study. The workshops will be offered twice every year when a new group of trainee therapists starts their outpatient therapies. The first workshop will provide a theoretical background in mindfulness, including descriptions of its roots in Theravada Buddhism, its first practical implications in MBSR, and the integration of mindfulness in the other third-wave approaches of CBT. Furthermore, formal mindfulness practices (specific techniques such as breathing meditation and body scan) and informal mindfulness practices (introducing mindfulness in everyday life by mindfully carrying out activities like showering, eating, and walking) will be described and conducted. In the 6-week interval between workshops one and two, participants will practice formal and informal mindfulness activities at home. The second workshop will specifically address the mindfulness experiences of participants, and suggestions for further improvements will be the focus. Additionally, to reduce the potential allegiance effects in relation to mindfulness interventions, all participating therapists will receive two regular workshops on relaxation techniques that specifically focus on PMR as part of their regular therapist-training program.

### Blinding, allegiance, and randomization

The focus of the current study is on the external validity and generalizability of the results to routine clinical practice. Consequently, according to the extension of the CONSORT statement concerning the criteria of a pragmatic randomized, controlled trial (Zwarenstein et al. 2008), no blinding concerning treatment conditions will be implemented in the current study. All participants will be informed about the general aims and procedures of the study. However, they will be blind concerning the specific hypotheses.

In our study, we will apply a crossed-therapist design in which a given therapist delivers the experimental and control conditions (Falkenstrom et al. 2013). This design includes specific limitations (e.g., the increased problem of allegiance effects (Falkenstrom et al. 2013)), but will be necessary to conduct the study in routine care. To address the potential problems of this design, we will control for allegiance effects with a specific instrument. Furthermore, all three treatment conditions will be introduced in a neutral way, and preparation in PMR will be as intensive as mindfulness preparation. Additionally, the crossed-therapist design allows researchers to address the issue of potential therapist effects (Baldwin and Imel 2013). More specifically, as efficacy varies across therapists, a crossed-therapist design allows researchers to control for these effects as the same therapists perform all of the different treatment conditions.

Treatment allocation will be performed by a blocked and stratified randomization process with a computerized random-number generator (www.random.org). Patients will be stratified according to their main diagnosis (depression or anxiety disorder) and then randomized by a balanced blocking procedure into the three treatment arms. Randomization will be conducted by an independent research assistant, while the other researchers have no access to the randomization list and process. According to the CONSORT statement (Altman et al. 2001), the people involved in the generation and implementation of the random treatment sequences will be completely separated. A CONSORT flow chart of the study design is depicted in Fig. 1.

